### Randomization and allocation concealment

Stratified-block randomization would be applied into the study, which will take each center as a stratification factor. Each eligible participant will be randomly assigned to either the intervention group or control group according to 1:1 equal proportion rule. The sequence of random allocation will be generated using the PLAN sentences of the statistical software SAS 9.3 (SAS institute Inc., Cary, NC, USA), by an independent statistician who will not be involved in this trial from the Center of Evidence Based Medicine, FJTCM. Also, the sequence of random allocation will be concealed to outcome assessors and the statistical analyst. Then, the eligible participants will be informed of their allocation result by the project manager via telephone after their baseline information has been assessed, and the therapists (including acupuncturist and cognitive therapists) will be notified of the allocation and arrange the allocated treatment directly for the patient.

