### Blinding

In this trial, both the outcome assessors and the statistical analyst will be blinded to the randomization allocation and will not be involved in performance of the interventions. It will be, nevertheless, impossible to blind the participants, acupuncturists, and cognitive therapists since they will perform the interventional protocols. In the meantime, a specified project manager will be assigned to be in charge of the random allocated sequence and blind code of allocation, in which the intervention group or control group will be replaced by the letter A or B. Random parameters would be kept in the blind codes, using sealed opaque envelopes to conceal random allocation. Unblinding will only occur once all the outcome data collection is completed at 36 weeks.

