### Statistical methods

All data will be analyzed using SAS version 8.2 (SAS institute Inc., Cary, NC, USA) by an independent blinded statistician. A statistical significance level of 0.05 will be used. For statistical description, continuous variables will be presented for each group using the mean ± standard deviation for normal distribution, and median and interquartile range for non-normal distribution. Categorical variables will be presented by using proportions with their standard error. In order to compare the primary and secondary outcomes between groups, measured at baseline, post-intervention and post-follow-up, the t-test or Mann–Whitney U test will be used for continuous variables and the Pearson chi-squared or Fisher’s exact test will be used for categorical variables. Non-parametric tests, Pearson chi-squared test, or Fisher’s exact test will be used for expressing changes in effect sizes of primary and secondary outcomes between groups before and after treatment, and during the follow-up period (at 12 weeks and 24 weeks).

To adjust the confounding influence if necessary, a general linear model or linear regression will be applied for dependent continuous variables, and a logistic regression model for dependent categorical variables. The analysis of the primary outcome will be expressed by using full analysis set with the principle of intention-to treat and the per-protocol set. The analysis of the secondary outcomes will be performed using the per-protocol set. The analysis of AE will be undertaken by using a chi-square test or Fisher’s exact test. Lastly, the economic evaluation will be assessed using cost-effectiveness analysis. Missing data will be imputed by the last observation carried forward rules.

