However, this protocol design also has potential limitations: for example, it is not a double-blinded, placebo-controlled trial. From the perspective of evidence-based medicine, randomized, double-blind, placebo-controlled trials are the best the trials that render the highest evidence quality, but their feasibility is a major difficulty in non-pharmacological research areas [65]. Considering the ethics and participants’ adherence, blinding seems difficult for acupuncture in a clinical study, thus randomized, double-blinded, placebo-controlled trials may be impossible. Considering these facts, this trial attempts to reduce possible bias through blinding both outcome assessors and data analyst. Further, potential spontaneous recovery at the early stage of stroke may have the confounding effects on the trial.

To conclude, this trial aims to evaluate, under strictly systemized operational and high quality practices, whether a therapeutic regimen of TCM rehabilitation can effectively improve cognitive functions recovery after stroke under strict standard operational practices. If this trial is successfully carried out and renders high quality evidence to support a therapeutic regimen of TCM rehabilitation for PSCI management, this low cost and feasible therapy could be implemented on a larger scale in clinical and community settings.

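### No single primary MMSE comparison is fixed: the named tests are unadjusted, centre is not used, baseline MMSE enters at most by subtraction, and a linear model is applied only on an undefined need

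*Protocol article*

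**What the plan says.** Four statements in the protocol article bear on this point.

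- **Visit scores (Statistical methods).** The comparison is introduced with "In order to compare the primary and secondary outcomes between groups, measured at baseline, post-intervention and post-follow-up", and the method is that "the t-test or Mann–Whitney U test will be used for continuous variables".
- **Changes (Statistical methods).** Non-parametric, Pearson chi-squared or Fisher's exact tests "will be used for expressing changes in effect sizes of primary and secondary outcomes between groups before and after treatment" and during follow-up. The t-test is not in this list.
- **Adjustment (Statistical methods).** "To adjust the confounding influence if necessary, a general linear model or linear regression will be applied" to continuous outcomes. The text does not say what makes adjustment necessary, which covariates enter, or whether the adjusted or the unadjusted result is primary.
- **Design.** Under Randomization and allocation concealment, the seven-centre trial uses stratified blocks, "which will take each center as a stratification factor". Table 1 has MMSE measured at baseline, 12 weeks and 36 weeks. The Sample size section bases the calculation on improvement in MMSE, using a formula for comparing two means.

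Under Blinding, "both the outcome assessors and the statistical analyst will be blinded to the randomization allocation", with the groups coded A and B.

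**The concern.** The analysis text does not match the rest of the design in three ways.

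1. **Centre.** It is a randomisation stratum but appears in none of the named comparisons. Between-centre variation then stays in the error term of the visit-score tests.
2. **Baseline MMSE.** It is collected on everyone. A test of change subtracts it and a test of visit scores leaves it out. Neither conditions on it.
3. **Estimand.** The trial is sized on a difference in mean improvement. The tests listed for change are rank or categorical tests, which do not estimate that difference. The t-test is assigned to visit scores, which is a different comparison.

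In addition, no result is designated primary. A visit-score test, a change test and an adjusted model could each be presented as the main MMSE result. What is at stake is some power, and a 5% error rate that is assured only if the choice among these is made beforehand.

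**Working it through.** **Inputs from the Sample size section:** reference change 3 points, SD 1.5, pilot figure 3.52 points, α = 0.05, power 90%, 173 per group, 20% dropout, 208 per group.

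**Assumptions not in the document:** two-sided testing, a baseline-to-follow-up correlation r of 0.5 to 0.7, and equal SDs at the two visits.

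**Step 1. Reproduce the plan's figure.** The formula is n = 2(u_α + u_β)²σ²/δ².
- δ = 3.52 − 3 = 0.52, two-sided: 2 × (1.96 + 1.2816)² × 1.5² / 0.52² = 174.9, so 175. This is close to 173.
- δ = 3.52 taken literally gives 4 per group, δ = 3 gives 6, and one-sided δ = 0.52 gives 143.

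So δ = 0.52 is inferred because it approximately reproduces 173. The article does not state it.

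**Step 2. Patients analysed.** 173 × 1.2 = 207.6, so 208 are recruited per group. If 20% are lost and leave the analysis, 208 × 0.8 = 166 remain. If the full analysis set keeps everyone through last observation carried forward, 208 are analysed. Both are shown, and any dilution from carrying values forward is ignored.

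**Step 3. SD under each analysis, holding the change SD at 1.5.**
- Single-visit score SD: 1.5 / √(2(1 − r)), which is 1.500 at r = 0.5 and 1.936 at r = 0.7.
- ANCOVA residual SD: score SD × √(1 − r²), which is 1.299 at r = 0.5 and 1.383 at r = 0.7.
- Variance ratio of ANCOVA to change score: (1 + r)/2, which is 0.75 at r = 0.5 and 0.85 at r = 0.7.

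**Step 4. Power for δ = 0.52 (two-sided t-test).**

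| Analysis | r | 166 per group | 208 per group |
|---|---|---|---|
| Change score | any | 88% | 94% |
| ANCOVA on baseline | 0.5 | 95% | 98% |
| ANCOVA on baseline | 0.7 | 93% | 97% |
| Raw week-12 score | 0.5 | 88% | 94% |
| Raw week-12 score | 0.7 | 68% | 78% |

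ANCOVA has the highest power in each column. The raw score falls below the change score only when r exceeds 0.5. These figures count only the gain from baseline MMSE. Any gain from centre is extra and is not quantified here.

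**Step 5. Type I error, simulated under no effect.** The simulation used 173 per arm, seven centres, blocks of 4, r of 0.5 or 0.7, an assumed centre intraclass correlation of 0.05 or 0.15, and 4,000 replicates per scenario (Monte Carlo error roughly 0.3 to 0.5 percentage points).
- Unadjusted t-test on the final score alone: 3.5–4.7%, lower with the larger centre effect.
- ANCOVA with baseline and centre alone: 4.2–4.9%.
- Smaller p-value of those two: 6.4–7.1%.
- Smallest p-value of six analyses (t and Mann–Whitney on final score and on change, ANCOVA with and without centre): 9.7–10.8%.

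The last two lines are upper bounds, because they assume the smallest p-value is always taken.

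**The case against.** The strongest reply has five parts.

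- **This is a condensed article, and covariate lists belong in an analysis plan.** That is fair for the list itself. It does not cover what is written: the unadjusted tests are named as the comparison and the model is made conditional. An analysis plan would have to override that text, not just complete it.
- **Baseline is used.** This stands in part. A reader might infer that the plan ignores baseline MMSE altogether. It does not, because changes are tested and the sizing rests on improvement. The supportable statement is that baseline is not a covariate.
- **The unadjusted tests are valid.** This stands. Used alone they are valid to conservative, and any inflation comes only from choosing among analyses.
- **The analyst is blinded.** This stands as a limit. With A/B codes it is hard to choose in favour of one arm, but A-versus-B p-values would still be visible. A reader might also infer that the adjustment decision follows an inspection of baseline balance. The article does not say when or how necessity is judged.
- **The power loss is small.** Against a change-score test it is a few percentage points. The 68% figure applies only if raw week-12 scores are primary, which the article does not fix and the Sample size section points away from. It is not the expected loss.

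A reader might further take the Discussion's remark that "potential spontaneous recovery at the early stage of stroke may have the confounding effects on the trial" to require adjustment for time since stroke. Randomisation balances spontaneous recovery in expectation, and time since stroke is not in the Baseline tests list, although the within-one-year entry criterion implies that onset is known. It is an optional covariate, and leaving it out is not an error.

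**Conclusion.** The point holds in this form. The stated analysis fixes no single primary MMSE comparison, leaves out the stratification factor, does not condition on baseline MMSE, and makes the one method that could do so depend on an undefined need. The change tests it lists do not estimate the quantity on which the trial was sized.

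The precision cost against a change-score test is about 5 to 7 percentage points of power at 166 per group and about 3 to 4 at 208 per group. It is larger only if raw week-12 scores are primary and r exceeds 0.5. The cost of the open choice is a type I error somewhere between the nominal 5% and an upper bound of about 6–11%, depending on how many analyses are in play. The correlation, the centre intraclass correlation, the block size and δ = 0.52 are assumptions or inferences. The direction of the precision result does not depend on the exact correlation within the range shown. This should be corrected, but it does not invalidate the trial.

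**What to change.** For the primary outcome, delete the condition on adjustment and name one primary model before unblinding: a linear model (ANCOVA, or the repeated-measures equivalent) of week-12 MMSE on arm, baseline MMSE and centre. Report the adjusted mean difference with its 95% confidence interval. Label the unadjusted t-tests and the rank tests as sensitivity analyses. Time since stroke may be added as a pre-specified covariate if it is recorded. Use the same form of model for the other continuous outcomes where their distribution allows. Reaction times and error counts may need a transformation or a different model.

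The cost is a change of wording in the protocol and analysis plan. Baseline MMSE and centre are already available for every patient, and neither the sample size nor the visit schedule changes.

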### Sample size

The sample size calculation is based on the improvement of MMSE scores, which is used as the primary effect indicators to estimate. According to the similar published articles [29], the mean difference in MMSE scores before and after treatment is three points, with a standard deviation of 1.5. According to our pilot study, a therapeutic regimen of TCM rehabilitation (CT + acupuncture) can probably improve the MMSE by 3.52 points on average compared to the control group. Improvement will be measured according to the same size of the estimation formula:1$$ \mathrm{n}=2\left[{\left({u}_{\alpha }+{u}_{\beta}\right)}^2{\sigma}^2\right]/{\delta}^2 $$

With a type I error of 5 % (α = 0.05) and 90 % power (β = 0.10), it is estimated that a sample size of 173 participants per group will be required. Considering a 20 % dropout rate during the study, a minimum of 416 total participants is needed to reach the target 208 participants per group.

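### Secondary outcomes are assigned to the per-protocol set alone, so their group comparisons are not protected by randomisation

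*Protocol article*

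**What the plan says.** Two consecutive sentences in the protocol article, Statistical methods, fix the analysis sets. For MMSE: "The analysis of the primary outcome will be expressed by using full analysis set with the principle of intention-to treat and the per-protocol set". For everything listed as secondary: "The analysis of the secondary outcomes will be performed using the per-protocol set". The same paragraph sets a general rule for incomplete data: "Missing data will be imputed by the last observation carried forward rules".

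Table 1 lists ten secondary measures: MoCA, TAP, WMS, TMT, Stroop, MBI, SF-36, FMA, fMRI and ERP. Only MoCA, MBI and SF-36 are repeated at 36 weeks. The other seven are measured at baseline and at the end of treatment. The Blinding section says that assessors and the analyst are blinded, while participants, acupuncturists and cognitive therapists are not.

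**The concern.** Randomisation makes the arms comparable as allocated. Once participants are removed for reasons that arise afterwards, that guarantee lapses unless the removals are unrelated to outcome or affect both arms alike. Blinded assessment does not help, because the selection concerns who is analysed and not how they are scored.

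The trial asks whether cognitive training plus acupuncture is better than cognitive training, and both participants and therapists know the allocation. Only one arm is needled, with stimulation to a sensation that includes pain, so reasons for leaving the regimen can differ by arm.

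The affected outcomes are not marginal. The Discussion presents domain-specific cognition as what sets this trial apart from earlier ones. MBI and SF-36 are the measures of daily living and quality of life. Of the four measures taken at 36 weeks, three would have no intention-to-treat analysis, although long-term effectiveness is a stated aim in the Abstract.

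**Working it through.** **Reading the text.** The two sentences on analysis sets stand side by side. The primary outcome has the "full analysis set with the principle of intention-to treat and the per-protocol set"; the secondary outcomes have one set only. The contrast makes this a stated choice, not a detail left to an analysis plan, and nothing elsewhere in the article changes it.

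**Plan figures.** The article gives no size for the per-protocol set and no planned effect for any secondary outcome, so there is no figure on this point to reproduce. The illustration uses only the enrolment target from Sample size: 173 × 1.2 = 207.6, rounded to 208 per group, and 2 × 208 = 416.

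**Illustration (assumptions not in the documents).** There is no true treatment effect. Each participant has a latent prognosis, standard normal, with correlation ρ to the outcome. In each arm the fraction p with the poorest prognosis is excluded. The expected mean of those kept, in SD units, is ρ × h(p), where h(p) = φ(z_p)/(1 − p). The spurious difference between arms is

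ρ × [h(p₁) − h(p₀)].

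Values of h:
- h(0.10) = 0.1755/0.90 = 0.195
- h(0.15) = 0.2332/0.85 = 0.274
- h(0.25) = 0.3178/0.75 = 0.424
- h(0.30) = 0.3477/0.70 = 0.497

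Differences: 25% versus 15% gives 0.424 − 0.274 = 0.150; 30% versus 10% gives 0.497 − 0.195 = 0.302. Multiplying by ρ gives the third column below. The last two columns come from 4,000 simulated trials with 208 per arm and a two-sided t-test at 0.05.

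| Excluded (arm 1 / arm 0) | ρ | Formula, SD | Simulated, SD | Type I error |
|---|---|---|---|---|
| 20% / 20% | 0 | 0 | 0.001 | 4.8% |
| 20% / 20% | 0.3 | 0 | −0.002 | 5.2% |
| 20% / 20% | 0.5 | 0 | 0.001 | 5.8% |
| 25% / 15% | 0 | 0 | 0.000 | 5.0% |
| 25% / 15% | 0.3 | 0.045 | 0.046 | 7.8% |
| 25% / 15% | 0.5 | 0.075 | 0.076 | 12.5% |
| 30% / 10% | 0 | 0 | −0.004 | 5.5% |
| 30% / 10% | 0.3 | 0.091 | 0.089 | 13.7% |
| 30% / 10% | 0.5 | 0.151 | 0.147 | 29.1% |

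Each scenario excludes 20% overall. That figure is borrowed from the dropout allowance only to set a scale. Swapping the arms reverses the sign. Bias needs both conditions: unequal exclusion and a link between exclusion and outcome.

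**Carried-forward values.** For TAP, WMS, TMT, Stroop, FMA, fMRI and ERP the only observation before week 12 is baseline. Carrying it forward records zero change for anyone not measured at week 12, while the Discussion warns of possible spontaneous recovery early after stroke. Changing the analysis set while keeping this rule would replace one problem with another.

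**The case against.** The strongest reply is that the trial's main conclusion is untouched: MMSE, on which the sample size rests, keeps an intention-to-treat analysis. That stands, and it limits the severity.

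Several stronger readings are tempting but go beyond the documents:

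- A reader might infer that the secondary analyses compare completers or adherers. The article does not define the set. It could turn on eligibility violations, attendance or missing visits, and the carry-forward rule might keep some participants without a final measurement.
- A reader might infer a heavier attendance burden in the acupuncture arm. Under Cognitive training and Acupuncture therapy, needling takes place during the same 30-minute session, five days a week for 12 weeks. Session time is equal; the needling differs. No adherence figures by arm are given.
- A reader might infer that the intervention will be flattered. Nothing in the documents fixes a direction.
- A reader might apply the 20% dropout allowance and say that about 83 of 416 participants are lost (0.20 × 416 = 83.2). That equates dropout with per-protocol exclusion, which the article does not do. Participants who leave before week 12 lack a later measurement in either set.
- A reader might object that the article does not say which set decides the MMSE result. That is commonly settled in an analysis plan and is not a fault here.

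It is also fair that fMRI and ERP serve partly to study mechanism, where an analysis of those treated as planned has a use. That supports a per-protocol analysis as an addition. It does not justify having no analysis as randomised for measures listed as secondary outcomes.

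**Conclusion.** The point holds. As written, every secondary outcome comparison rests on a subset presumably selected after randomisation, in a trial where selection could differ by arm. Adverse events and the economic evaluation are outside the point, since the article names no set for them.

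The bias is possible, not shown. In the illustration its magnitude runs from 0 to about 0.15 SD in either direction, with type I error from the nominal level up to about 29%. These figures rest on assumed exclusion rates, on exclusion of those with the poorest prognosis and on correlations of 0 to 0.5.

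It would be tempting to express 0.15 SD as a share of the planned effect. The documents do not support that. Sample size states an MMSE gain of 3.52 points over control with an SD of 1.5, which is 3.52/1.5 = 2.35 SD. The stated 173 per group is approached only with a difference of 3.52 − 3 = 0.52 (0.35 SD), which the article never states: 2 × (1.96 + 1.28)² × 1.5²/0.52² = 174.7. Either way this is an MMSE effect, and none is given for any secondary outcome.

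Severity: should-fix.

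**What to change.** Replace the sentence on secondary outcomes so that all secondary efficacy outcomes are analysed in the full analysis set, by allocated arm. Keep the per-protocol analysis as supportive only, with its membership rule fixed before unblinding.

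Deal with missing values at the same time. For the seven measures taken only at baseline and week 12, use all observed data in a baseline-adjusted or likelihood-based analysis and do not rely on the carried-forward baseline value. The same approach suits MoCA, MBI and SF-36, which have two later visits. This does not recover participants with no later measurement: it assumes that their absence is explained by the data in the model. It does retain everyone who was measured but would be excluded by a per-protocol rule.

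The cost is a few sentences and somewhat more analysis work, with no new visits or measurements. Estimated effects may turn out smaller.

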**Discussion:**

This protocol presents an objective design of a multicenter, large sample, randomized controlled trial that aims to put forward a lower cost and more effective therapy, and confirm the long-term effectiveness of a therapeutic regimen of TCM rehabilitation for PSCI through subjective and objective assessments, as well as highlight its economic advantages.

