### Outcome measures

In this study, all the primary and secondary outcomes measures will be tested at baseline (−2 to −1 week) and after the intervention period (12 weeks). After follow-up (36 weeks), the cognitive function, quality of life, and ADL outcomes (MMSE, MoCA, SF-36, and MBI) will also be evaluated. All outcome assessments will be independently performed by experienced and blinded assessors. A summary of all the measures in the trial is shown in Table 1.

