A notable difference between our study and former studies is that this trial will investigate, some domain-specific cognitive functions as well as general cognitive state. According to one article, patients with PSCI will mainly exhibit dysfunctions in attention, memory, and executive function [6]. To evaluate domain-specific cognitive function various measures were selected: the TAP to assess attention, the WMS-RC to evaluate memory, and the TMT and Stroop test to measure executive function. In this study, detailed information on performance in multifarious tasks designed for CT will be recorded, allowing an insightful outcome analysis by taking into account the severity of and inter-relationships among the cognitive deficits in various domains. Besides, fMRI and ERPs will be included in this trial as objective indicators of cognitive function [59–61]. Since many stroke patients who suffer from PSCI and movement disorders cannot understand and/or perform tasks adequately, resting-state fMRI was chosen over tasking-state fMRI for this study [62]. Meanwhile, ERP P300 and resting-state fMRI make it possible to provide a potential mechanism for the therapeutic effects of this trial’s approach, and to further explore the relationship between cognitive functional networks and brain structure, thus allowing the researchers to investigate the relationship between subjective scales and objective indicators.

Adhere to the SPIRIT guidelines, a prospective, multicenter, large sample, randomized controlled trial with blinded assessments has been designed [63]. This protocol design has several strengths: (1) it is a multicenter trial that will be carried out in seven inpatient and outpatient stroke rehabilitation units, which enhances the study’s external validity and sample representativeness; (2) to guarantee quality, all staff in the study are required to complete training on standard operating procedures of the study protocol before recruiting; (3) this study is centrally randomized to guarantee adequate allocation concealment and blinded assessment of results [64]; (4) a 12-week intervention and 24-week follow-up assessment can provide reliable long-term effect evidence for a therapeutic regimen of TCM rehabilitation treatment and its health economics in PSCI clinical practice.

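### All ten secondary outcomes are assigned to the per-protocol set alone, so only the primary MMSE has an intention-to-treat comparison

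*Protocol article*

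**What the plan says.** Under Statistical methods, the protocol article sets two different rules in consecutive sentences.

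- Primary outcome (MMSE): "The analysis of the primary outcome will be expressed by using full analysis set with the principle of intention-to treat and the per-protocol set".
- Secondary outcomes: "The analysis of the secondary outcomes will be performed using the per-protocol set".

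No other section names a different set for the secondary outcomes. Table 1 lists ten of them: MoCA, TAP, WMS, TMT, Stroop, MBI, SF-36, FMA, fMRI and ERP. On the week-36 visit, Outcome measures says: "After follow-up (36 weeks), the cognitive function, quality of life, and ADL outcomes (MMSE, MoCA, SF-36, and MBI) will also be evaluated".

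The article leans on these measures. The abstract says that the trial will "confirm the long-term effectiveness of a therapeutic regimen of TCM rehabilitation for PSCI through subjective and objective assessments". The main Discussion presents domain-specific testing as a feature that sets the trial apart ("the TAP to assess attention, the WMS-RC to evaluate memory, and the TMT and Stroop test to measure executive function") and adds that "fMRI and ERPs will be included in this trial as objective indicators of cognitive function". Every measure in those last two quotes is secondary.

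**The concern.** Being in the per-protocol set depends on what happens after randomisation. If the arms lose different kinds of patient from that set, a between-arm difference can reflect who stayed and not what the treatment did.

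Two features make that possible here. The Blinding section calls it "impossible to blind the participants, acupuncturists, and cognitive therapists", so the decision to stop, or to skip sessions, is made with the arm known. And although both arms train five days a week for 12 weeks (12 × 5 = 60 sessions), only one arm also has needling at those sessions. Blinded assessors and a blinded analyst do not repair this, because the selection does not depend on how the outcome is scored.

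At stake are the comparisons of attention, memory, executive function, motor function, daily living and quality of life, the imaging and electrophysiology results, and the MoCA, SF-36 and MBI results at week 36. A claim on any of these would rest on a selected subgroup, with no randomised analysis beside it.

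**Working it through.** The plan gives no figure for this point to reproduce. The check is a count, followed by a calculation of how large the bias could be.

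**Step 1. Count** (Table 1, Outcome measures, Statistical methods)

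| Outcomes | Number | With an intention-to-treat analysis |
|---|---|---|
| Primary (MMSE) | 1 | 1 |
| Secondary | 10 | 0 |
| Assessed at week 36 (MMSE, MoCA, SF-36, MBI) | 4 | 1 |

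**Step 2. Per-protocol bias by simulation**

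From the document: 208 per group and 20% dropout (Sample size), significance level 0.05 (Statistical methods). Assumed, because the document gives no figure: the share excluded from the per-protocol set, and how exclusion relates to outcome.

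The outcome is standard normal in both arms, so there is no true effect. The chance of exclusion follows logit(p) = a − b × outcome, where b is the slope per SD and a is set to give the stated share. The arms are compared by a two-sample t-test.

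| Exclusion, acupuncture arm | Exclusion, control arm | Per-protocol bias | False positives |
|---|---|---|---|
| 20%, slope 1 | 20%, slope 1 | 0 | 5% |
| 20%, slope 1 | 10%, slope 1 | 0.08 SD | about 13% |
| 20%, slope 0.5 | 20%, random | 0.10 SD | 14% |
| 20%, slope 1 | 20%, random | 0.17 SD | about 36% |

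The bias favours acupuncture in these rows only because of how the assumptions were set. Exchanging the arms reverses the sign.

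**Step 3. Check with a different model**

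Let retention depend on a latent normal variable with correlation ρ to outcome. If a share e is excluded, the mean of those retained is ρ × φ(z_e)/(1 − e), with z_e the normal quantile of e. For 30% versus 10% excluded and ρ = 0.5:

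- Bias = 0.5 × (0.348/0.70 − 0.175/0.90) = 0.5 × (0.497 − 0.195) = 0.15 SD.
- Standard error = √(1/145.6 + 1/187.2) = 0.110.
- Rejection = Φ(0.151/0.1105 − 1.96) + Φ(−0.151/0.1105 − 1.96) = 27.6%.

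Over ρ from 0.2 to 0.5, the ranges are:

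- 30% versus 10% excluded: bias 0.06 to 0.15 SD, rejection 8.5% to 27.6%.
- 25% versus 15% excluded: bias 0.03 to 0.08 SD, rejection 5.9% to 10.4%.
- 20% in each arm by the same mechanism: no bias.

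**Step 4. What the full analysis set would do**

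If every excluded patient is still assessed, the full set rejects about 5% of the time in all the Step 2 scenarios.

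If the excluded patients are dropouts, Statistical methods fills them in by last observation carried forward. Take their change as zero. An arm's mean change is then (1 − e) × (μ + m), where μ is the mean improvement in SD units and m is the shift among those retained. I let μ run from 0 to 2. The upper end is the 3 points over an SD of 1.5 in Sample size (3/1.5 = 2), which is for the MMSE.

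- With 20% out of each arm, the bias is 0.8 × the per-protocol bias. For slope 1 in one arm only, that is 0.8 × 0.17 = 0.14 SD, with about 22% to 35% false positives. For slope 0.5 in one arm only, false positives are about 10% to 15%.
- With 20% versus 10% out and slope 1 in both arms, the bias is about 0.06 − (0.20 − 0.10) × μ. It runs from +0.06 SD at μ = 0 to −0.14 SD at μ = 2, with false positives from about 7% to 24%.

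**The case against.** The strongest reply is that the harm is conjecture. The document gives no exclusion rates by arm, and if exclusion works identically in both arms the bias is zero. Acupuncture is given during the same 30-minute training session, so no extra visits are described, and unblinded controls might just as well leave because they were not given needling. This stands: differential exclusion and its direction are a risk, not a fact. A reader might infer that the secondary results will be biased towards acupuncture. The document does not support that.

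A second reply is that the full analysis set is no cure. This also stands in part. It would be tempting to set 36% false positives against 5%, but Step 4 shows that this contrast requires excluded patients to be assessed. Seven secondary measures (TAP, WMS, TMT, Stroop, FMA, fMRI and ERP) are taken only at baseline and week 12. For a patient missing at week 12, last observation carried forward means carrying the baseline forward.

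A third reply is that the long-term result is protected, because the MMSE is measured at week 36 and has an intention-to-treat analysis. That is correct for the MMSE. Three of four counts instruments, not weight of evidence, so it does not mean that the whole long-term claim lacks a randomised comparison.

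Finally, the criteria for the per-protocol set may stand in a document not shown. They could limit how selective the set is, but the choice of that set for the secondary outcomes is stated outright here and is not a detail left for later.

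**Conclusion.** The point holds as a stated rule that should be changed. All ten secondary outcomes, three of them also assessed at week 36, have only a per-protocol comparison, in a trial where patients and therapists know the arm. Randomisation does not protect those comparisons if reasons for leaving the set differ by arm and relate to outcome.

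The possible size, under assumed mechanisms with 208 per arm and no true effect, runs from no bias to 0.17 SD with about 36% false positives. The upper end needs outcome-dependent exclusion in one arm and random exclusion in the other, which is an extreme case.

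Two limits apply. The primary comparison is untouched at week 12 and at week 36, so this should be fixed but does not undermine the trial. And a reader might extend the point to the economic evaluation. The article names no analysis set for it, so there is nothing stated there to correct.

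**What to change.** Replace the sentence on secondary outcomes with: *All secondary outcomes are analysed in the full analysis set by randomised group, using all observed data, including data from participants who did not keep to protocol; per-protocol results are supportive only.*

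This would take secondary measures with a comparison by randomised group from 0 of 10 to 10 of 10, and week-36 measures from 1 of 4 to 4 of 4. It needs no new patients or measurements: the same analyses are run on a larger set. It should be made before the unblinding that the Blinding section places after the last week-36 data, because a set chosen after the results are known would not be credible.

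There are two costs. Estimated effects may look smaller once patients who did not keep to protocol are included. And results for patients with no later assessment will still depend on the missing-data method, so the change gives its full benefit only where those who leave the protocol are still assessed.
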